### Intervention

#### Risk factor modification structured Programme

The risk factor modification intervention programme is a 12-week intensive lifestyle programme. This is a nurse-led, community-based, lifestyle and risk factor modification intervention modelled on the European Society of Cardiology demonstration project, a large clinical trial called EuroAction [30]. The programme includes:
Phase 1: Initial individualised assessment by the multidisciplinary team (MDT) will include previously mentioned baseline assessment in addition to the following:
Dietician will assess, current eating habits and food diaryExercise specialist will assess 7-day activity recall, barriers to exercise, 7-day pedometer and Functional Capacity TestPhase 2: The intervention including:
Weekly exercise class and educational workshops.Serial blood pressure, body mass index, waist circumference, glucose and lipid measurements with goal setting.Weekly MDT meetings.Targeted and protocol-based pharmacotherapy to support lifestyle changes.

#### Standard healthcare

The control group will receive the standard healthcare advice provided to PAD patients in the outpatient PAD clinic. In this study, standard care will be conducted by the researchers which include:
Advising patients to quit smoking, regular exercise and healthy eating, but neither structured intervention nor organised cessation plans will be addressed.Non-specific interventions, such as providing patients with educational material on general health problems.

#### Twelve-week assessment

On completion of the 12 weeks in both groups, patients are reassessed for risk factors, therapeutic management and lifestyle changes similar to baseline.

#### One-year assessment

Similar to the baseline and 12-week assessment, in addition to clinical outcomes assessment, the following are included:
If the patient underwent a major amputation and level of amputationIf required a revascularisation procedure.Any residual stenosis of more than 30% [17]If developed a major adverse cardiovascular event (MACE) or major adverse limb event (MALE)Health-related quality of lifeCost-effectiveness of the programme

### Endpoints

#### Primary endpoint

Achieving target improvement in lifestyle risk factors at 12 weeks and at 1 year. Target improvement will be considered if the patient achieves any one or more of the following:
Smoking cessationBMI 20–25 (kg/m^2). BMI is calculated by dividing body weight in kilogrammes by the square of height in metersHbA1c less than 7%Total cholesterol less than 5.0 mmol/L

Patients will be reassessed for the primary endpoint at 1 year. If they fail the criteria by which they were deemed at 12 weeks to have achieved the primary endpoint, they will then be considered to not have achieved the 1-year primary endpoint.

We will report the primary endpoint for both time points.

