### Randomisation

After meeting the inclusion criteria, screened patients will be randomised to one of two treatment arms. One arm will receive the 12-week intensive risk factor modification intervention programme. The control arm will be provided with standard care in the outpatient PAD clinic. This is an intention to treat designed study, where patients are analysed as randomised. Each screened patient will be given a unique screening number.

Screened patients will be randomised in a 1:1 ratio of study intervention: control according to a randomisation scheme. The randomisation scheme will be produced using the PROC PLAN® procedure of the SAS®software package (version 9.2.2) using a simple randomisation strategy. The scheme will be concealed from all patients and study personnel until after database lock.

Patients will be allocated to intervention via an automated telephone system, which will not deliver the randomised allocation except after registering the subject screening number. Each screened patient who is recruited to the trial will be given a unique patient trial number.

The statistician will remain blinded to the treatment allocation until all the data have been analysed to minimise bias. Outcome assessors and data analysts will be blinded; however, in the event of an adverse event outcome, assessors will be unblinded.

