### Sample size calculation

For sample size calculation, the EUROACTION study [30] was used to estimate the coefficient of variation for sample proportions.

Data from the EUROACTION [30] study suggest that 12-week intervention response rates for the primary endpoint of 54.8% (intervention programme) and 35.6% (usual care). Eighty percent statistical power and an alpha level of 5% were chosen. A two-sample comparison of proportions sample size calculation was implemented.

With these parameters, the G*Power [31] software yields a trial with a maximum sample size of 208 patients completing the intervention (104 per intervention group).

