### Statistical analysis

All data will be analysed according to the intention to treat principle. The primary outcome, the achievement of treatment goals for PAD risk factors between both groups at 12 weeks and 12 months will be compared using chi-square or Fisher’s exact where appropriate. Secondary outcomes including time to event will be assessed using Kaplan-Meier survival curves and log rank test. An exact 95% confidence interval will be applied for the difference between intervention groups in terms of PAD risk factor reduction.

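### Two primary time points share one unsplit 5% alpha, with no success rule or test order, so the stated 5% and 80% cannot both describe the primary claim

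*Protocol article*

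**What the plan says.** All references are to the protocol article.

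- **Primary endpoint:** "Achieving target improvement in lifestyle risk factors at 12 weeks and at 1 year". The 1-year endpoint is scored separately: a patient who no longer meets the criteria that counted at 12 weeks is a failure at 1 year. The section ends: "We will report the primary endpoint for both time points". The abstract also places the primary outcome at 3 and 12 months.
- **Statistical analysis:** goal achievement "between both groups at 12 weeks and 12 months will be compared using chi-square or Fisher’s exact where appropriate".
- **Sample size calculation:** "Eighty percent statistical power and an alpha level of 5% were chosen". The rates are "12-week intervention response rates for the primary endpoint of 54.8% (intervention programme) and 35.6% (usual care"), and the result is a "maximum sample size of 208 patients completing the intervention (104 per intervention group"). No 1-year rate is given.

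No section names one time point as decisive, orders the two tests, divides the alpha, or says whether the trial succeeds on either result or only on both.

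**The concern.** The endpoint and analysis sections set up two primary comparisons, while the sample size section budgets for one. The programme lasts 12 weeks, so an effect seen only at its end and an effect still present at 1 year are different claims. As the text stands, either could be labelled a positive primary result, and the choice of which one decides could be made after the data are seen. The error rate and the power attached to the trial's main conclusion therefore depend on a rule that has not been written down.

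**Working it through.** **Inputs.** From the sample size section: p1 = 0.548, p2 = 0.356, alpha 0.05, power 0.80, 104 per arm. Allocation is 1:1 (Randomisation). Sidedness is not stated. The correlation r between the two test statistics is not given either, so it is varied as an assumption.

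**Step 1: reproduce the plan's figure.** The difference is 0.192 and the pooled rate is (0.548 + 0.356)/2 = 0.452.

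n per arm = [1.960·√(2·0.452·0.548) + 0.842·√(0.548·0.452 + 0.356·0.644)]² / 0.192²
= [1.960·0.7038 + 0.842·0.6906]² / 0.03686
= 104.3, rounded up to 105.

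The arcsine formula gives 104.1. A one-sided test would give 83. The stated 104 per arm is therefore one two-sided 5% test at one time point.

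Power at 104 per arm: the standard error is √(2·0.452·0.548/104) = 0.0690 under the null and 0.0677 under the alternative. Φ[(0.192 − 1.960·0.0690)/0.0677] = Φ(0.838) = 79.9%.

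**Step 2: either time point counts as success.** Each test is taken at two-sided 5%. Family-wise error = 1 − P(|Z1| < 1.96 and |Z2| < 1.96), with (Z1, Z2) bivariate normal with correlation r. At r = 0 this is 1 − 0.95² = 9.75%.

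**Step 3: both time points required.** Joint power = P(Z1 < 0.838 and Z2 < 0.838) with the same r, assuming the same rates and numbers at 1 year as at 12 weeks. At r = 0 this is 0.799² = 63.8%.

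| Assumed r | Either suffices: two-sided error | Both required: joint power |
|---|---|---|
| 0 | 9.75% | 63.8% |
| 0.5 | 9.1% | 68.6% |
| 0.7 | 8.35% | 71.2% |
| 0.8 | 7.8% | 72.8% |
| 0.9 | 7.0% | 74.9% |
| 0.95 | 6.5% | 76.3% |

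Counting only false positives that favour the programme, the either-suffices error is 4.9% at r = 0 and 3.5% at r = 0.9, against 2.5% for one test.

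**Step 4: what r might be.** Assume a 12-week rate of 35.6% in both arms, 50% to 90% of achievers retained at 1 year, and 0% to 20% of the others becoming achievers. The correlation is then about 0.31 to 0.92 and the error 6.8% to 9.5%. Simulated chi-square tests with 104 per arm, over six such scenarios at 12-week rates of 35.6% and 45.2%, gave 7.2% to 9.2%.

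**Step 5: cost of the alternatives.** Splitting alpha into 2.5% and 2.5% lowers 12-week power at 104 per arm to Φ[(0.192 − 2.241·0.0690)/0.0677] = Φ(0.551) = 70.9%; 127 per arm (254 in total) would restore 80%. A fixed sequence starting at 12 weeks leaves the 79.9% unchanged.

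**The case against.** **The either-suffices rule and the 5% per test are inferred.** This stands. A reader might infer that the plan declares success on either result, each tested at 5%. No sentence says so, and the endpoint wording can also mean that both are needed. Separate scoring and separate reporting make two separate endpoints the likelier reading, but not the stated one. The alternative does not rescue the plan, because the stated power then no longer holds.

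**The size of the inflation is not known.** This also stands. A reader might put the error at 8% to 10%, but that needs a correlation of about 0.77 or less. The documents give none, and the rule carrying 12-week criteria forward to 1 year, with lasting criteria such as HbA1c, could push it higher.

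**Both results will be reported.** This commitment limits the harm: a short-lived effect could not be hidden beside its 1-year result. What remains open is which result carries the primary conclusion.

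**The test order may be in a full protocol or SAP not shown.** This is possible and lowers the severity. But the article itself fixes two primary time points, the tests and one alpha, and these do not fit together as published.

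**Conclusion.** The concern holds as an unstated success rule across two primary time points, not as a demonstrated error rate. The sample size supports one two-sided 5% test at 12 weeks with 79.9% power.

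- If either time point suffices, the family-wise error exceeds 5% and is at most 9.75%, or about 6.5% to 9.75% for r from 0.95 down to 0.
- If both are required, the error is not inflated but power is about 64% to 76% over the same range. It is lower still if the effect wanes by 1 year.

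Both ranges rest on an assumed correlation and on each test being run at two-sided 5%; the power range also assumes that the 12-week effect persists. Under neither rule do the stated 5% and 80% both describe the primary claim. Severity: should fix.

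**What to change.** Before unblinding, state a fixed sequence. Test the 12-week comparison first at two-sided 5%. Test 1 year at two-sided 5% only if 12 weeks is significant; otherwise report 1 year as an estimated difference with a 95% confidence interval. Report both time points in every case. Add to the sample size section that the 80% power applies to the 12-week comparison only.

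The cost is a short protocol amendment which, under the article's own procedure for important modifications, goes to the ethics committee and is notified to the registries and the journal. It needs no extra patients and loses no 12-week power. The price is that the 1-year result has no confirmatory status if 12 weeks fails. If the sponsor prefers to require both time points or to split the alpha, either rule is coherent, but the trial must then be re-sized or the lower power stated.

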### Eligibility criteria

#### Inclusion criteria

Aged 18 years or moreProvide written informed consentPAD: diagnosed by at least one of the following:
Ankle-brachial index of less than 0.90 in at least one lower extremity [9]Toe brachial index of less than 0.60 [9]Evidence of arterial occlusive disease in one lower extremity detected by duplex ultrasonography, computed tomographic angiography, or magnetic resonance angiography [9]Symptomatic PAD (Rutherford category 2 and above [19])Patients should have at least one of the following risk factors:
Blood pressure > 140/80 mmHgFasting blood sugar (FBS) > 53 mmol/molGlycosylated haemoglobin (HbA1c) > 7%Total cholesterol > 5 mmol/LLow-density lipoprotein (LDL) cholesterol > 2.6 mmol/LTriglycerides > 1.7 mmol/LHigh-density lipoprotein (HDL) < 1.0 mmol/L in men and < 1.2 mmol/L in womenPhysical activity less 30 min for 5 days per weekBody mass index (BMI) > 25 kg/m^2^Waist circumference > 80 cm in women, and > 94 cm in menCurrent smoker or exposure to tobacco in any formUnhealthy diet, Mediterranean diet score less than 10 points

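### Three of the four primary endpoint items do not require the factor to be off target at baseline, so patients can be successes at entry and the planned 80% power is unreliable

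*Protocol article*

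**What the plan says.** The Primary endpoint section names the endpoint "Achieving target improvement in lifestyle risk factors at 12 weeks and at 1 year" and then gives the scoring rule: "Target improvement will be considered if the patient achieves any one or more of the following". Four items follow: smoking cessation, BMI 20–25 kg/m², HbA1c below 7%, and "Total cholesterol less than 5.0 mmol/L". The only longitudinal condition concerns one year: a patient who no longer meets the criterion that counted at 12 weeks is a failure at one year. That rule looks back to 12 weeks, not to baseline.

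Under Inclusion criteria, "Patients should have at least one of the following risk factors". Twelve are listed. Four mirror endpoint items (HbA1c, total cholesterol, BMI, smoking). Eight do not: blood pressure, fasting blood sugar, LDL, triglycerides, HDL, physical activity, waist circumference and diet score.

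The Sample size calculation section takes from an earlier cardiac prevention trial "12-week intervention response rates for the primary endpoint of 54.8% (intervention programme) and 35.6% (usual care", and arrives at 104 completers per arm. "Eighty percent statistical power and an alpha level of 5% were chosen". The Statistical analysis section compares the arms by chi-square or Fisher's exact test and names no baseline term. Change from baseline in BMI, HbA1c and total cholesterol appears only under Secondary endpoints.

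**The concern.** The endpoint is called an improvement, but three of its four items can be scored without any improvement. To be a non-success on day 0, a patient must be off target on BMI, HbA1c and cholesterol all at once. Someone who enters because of blood pressure, inactivity or diet and whose HbA1c is below 7% already meets the rule. So does someone who enters with high cholesterol and HbA1c below 7%.

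Such patients raise the success rate in both arms alike and shrink the difference that the programme can produce. At stake are the stated power and the reading of the result. A null finding could reflect the scoring rule rather than the programme, and a high success rate in either arm could not be read as the rate of improvement.

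**Working it through.** **Inputs.** From Sample size calculation: p₁ = 0.548, p₂ = 0.356, alpha 5%, power 80%, 104 per arm. From Randomisation: 1:1 allocation. Sidedness is not stated. Two-sided is assumed because it reproduces the plan's figure, whereas one-sided gives 83 per arm.

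**1. The plan's own figure.** With pooled variance under the null, n per arm = [1.960·√(2p̄(1−p̄)) + 0.842·√(p₁(1−p₁) + p₂(1−p₂))]² / (p₁−p₂)².
- p̄ = 0.452, so the first root is √0.4954 = 0.7038.
- The second root is √(0.2477 + 0.2293) = 0.6906.
- n = (1.3795 + 0.5812)² / 0.192² = 3.8445 / 0.03686 = 104.3, rounded up to 105.
- Power at 104 per arm is 79.9%.

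The planned size therefore reproduces (210 against 208). The arithmetic is sound; the question is whether the rates suit this endpoint.

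**2. What a 35.6% control rate implies.** Under an any-of-four rule, every non-success is off target on BMI, HbA1c and cholesterol together. Non-successes are 1 − 0.356 = 64.4% of controls (taking all as assessed). So at least 64.4% of controls must be off target on all three at 12 weeks, and in particular at least 64.4% must have HbA1c of 7% or more. This bound holds whatever the correlation between items. The Inclusion criteria do not require diabetes, or any of these three factors to be off target.

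**3. Effect on power.** The document does not give the share s of patients already at target on at least one item at entry, so a range is used. Assumptions: those patients stay at target in both arms, and the rest respond at the planned rates. Then p = s + (1−s)·0.548 against s + (1−s)·0.356, and the difference is (1−s)·19.2 percentage points.

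| s | Intervention | Control | Power at 104 per arm | n per arm for 80% |
|---|---|---|---|---|
| 0% | 54.8% | 35.6% | 80% | 105 |
| 10% | 59.3% | 42.0% | 71% | 131 |
| 30% | 68.4% | 54.9% | 51% | 205 |
| 50% | 77.4% | 67.8% | 34% | 338 |
| 70% | 86.4% | 80.7% | 20% | 649 |
| 90% | 95.5% | 93.6% | 9% | 2205 |

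**4. How s could arise.** This is illustration only, with assumed shares at target and independent items.
- HbA1c 30%, cholesterol 20%, BMI 10%: s = 1 − 0.7·0.8·0.9 = 50%.
- HbA1c 60%, cholesterol 40%, BMI 20%: s = 1 − 0.4·0.6·0.8 = 81%.

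Three modest shares add up quickly under an any-of rule, but none of these inputs comes from the document.

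**The case against.** Several points on the other side have weight.

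- **The wording implies change.** The section speaks of improvement and of achieving targets, smoking cessation is itself a change item, and the full protocol behind the article may spell this out. That stands as far as it goes. But the article fixes the scoring rule, and nothing in that rule puts a change requirement on the other three items.
- **Randomisation balances patients at target.** This is true in expectation, so there is no bias and no inflation of type I error. It does not prevent dilution.
- **The power model is one scenario.** Patients at target may drift, and at one year those who lose their 12-week criterion count as failures, so maintenance may differ by arm and these patients are not wholly uninformative. The rest may also respond at other rates than planned. The table is therefore a sensitivity range, not a forecast.
- **The eight non-endpoint factors are not all unrelated to the endpoint.** LDL and waist overlap with cholesterol and BMI, and fasting blood sugar is given in mmol/mol, a unit used for HbA1c. This does not change the conclusion, since one factor is enough for entry.

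A reader might go further and infer that most patients are successes at entry and that the trial cannot show a difference. The document supports neither. It gives no baseline distribution, so the majority claim is plausible but unproven. Power is reduced rather than removed: it is still 51% at s = 30%, and it would be higher if the effect in the remaining patients were larger.

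A reader might also argue that 35.6% requires each item to be at target in only about 10% of patients. That figure, 1 − 0.644^(1/4) = 10.4%, depends on independence; with full overlap each item could be as high as 35.6%. The 64.4% bound does not need that assumption.

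**Conclusion.** The point holds as a defect of definition. Patients can be scored as having improved on day 0 in either arm, because three of the four items lack an off-target-at-baseline condition and entry is not tied to the endpoint items. The comparison stays unbiased but is diluted. The 54.8% and 35.6% planning rates, and with them the 80% power, are unreliable for this endpoint.

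The definitional gap is certain from the text; its size is not. Under the model above, even s = 10% takes power to about 71%, and s = 50% takes it to about 34%. These figures rest on an assumed s, on patients at target staying there, and on the rest responding exactly as planned.

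**What to change.** 1. **Definition.** Count a patient as a responder at a visit if at least one of the four factors that was off target at baseline is at target at that visit. State how never-smokers score on the smoking item.
2. **Analysis set.** Keep all randomised patients in the intention-to-treat report. Base the primary comparison on those with at least one of the four factors off target, using values recorded before randomisation (screening) or obtained before allocation is known. This matters because the section Baseline, prior to intervention has randomised patients undergo the full assessment, and patients will know their arm. If attendance there differed by arm, a subset built on those values could be affected by allocation. Entry needs only one factor, so check whether screening records hold all four for every patient.
3. **Entry.** For patients still to be recruited, require at least one of the four endpoint factors to be off target.
4. **Power.** Restate it from the blinded pooled response rate under the new definition, with the assumed difference stated. The planned rates should not be carried over unchecked.

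Cost: no new measurements, since BMI, HbA1c, lipids and smoking status are already collected at baseline. It does need a protocol amendment with ethics and registry notification. The primary analysis set becomes somewhat smaller, eligibility will be mixed across a recruitment period that began on 1 June 2018, and the restated power may be less favourable. Narrowing the primary comparison also departs from the present intention-to-treat wording, so the amendment should say so openly.

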## Methods

### Study design

This is a randomised, parallel group, active-control trial to compare the effectiveness of the risk factor modification intervention programme to standard healthcare in a tertiary vascular care centre, in the reduction of the prevalence of modifiable risk factors in PAD patients.

This trial will randomise patients with PAD in an equal ratio to one of two treatment arms. One arm will be randomised to undergo a risk factor modification intervention programme at a community-based centre. The other arm will be provided with standard healthcare advice, in the outpatient PAD clinic in a tertiary referral vascular centre. Patients randomised into the risk factor modification intervention programme will have the intervention administered for 12 weeks. Patients will then be followed for 12 months to determine further PAD outcomes. The participant flowchart through the study is shown in Fig. 1. SPIRIT figure for this trial is given in Fig. 2.

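### The 1-year primary endpoint scores patients with the same 1-year status differently, depending on which targets they met at 12 weeks

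*Protocol article*

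**What the plan says.** The Primary endpoint section of the protocol article names both time points in one definition: "Achieving target improvement in lifestyle risk factors at 12 weeks and at 1 year". The test is then given without distinction between visits: "Target improvement will be considered if the patient achieves any one or more of the following". The four targets are smoking cessation, BMI within a range, HbA1c below a limit and total cholesterol below a limit.

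The next paragraph reassesses patients at 1 year and adds a condition for those who had responded: "If they fail the criteria by which they were deemed at 12 weeks to have achieved the primary endpoint". The consequence for such patients is a 1-year failure, whatever else they have achieved. The rule makes no exception for a patient who meets a different target at 1 year. It does not say how patients who met several targets at 12 weeks are judged, and it sets no condition on 12-week non-responders.

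The Statistical analysis section compares the arms on this outcome at both 12 weeks and 12 months, by chi-square or Fisher's exact test.

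**The concern.** Read literally, the section scores 1-year success in two ways. A 12-week non-responder needs any one of the four targets at 1 year. A 12-week responder must still hold the targets met at 12 weeks, and meeting another one does not help.

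The result is not 1-year status, because it depends on the 12-week result. Nor is it durability, because patients who first respond after 12 weeks count as successes. Which test a patient faces is settled after randomisation, by a response that the programme is designed to raise. The arms are therefore not held to the same test in the same proportions, in a comparison that the protocol calls primary.

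**Working it through.** **Inputs from the protocol article.** Any-of-four definition and 1-year rule (Primary endpoint). 12-week response rates of 54.8% and 35.6%, 80% power, 5% alpha and 104 per arm (Sample size calculation). Sidedness is not stated and is taken as two-sided.

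**Inputs that the documents do not give.** How often each target is met, how often it is lost by 1 year, and how often another replaces it. These are assumptions below.

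**1. The plan's own figure.** Pooled-variance formula, mean rate 0.452:

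n = [1.960 × √(2 × 0.452 × 0.548) + 0.842 × √(0.548 × 0.452 + 0.356 × 0.644)]² / 0.192² = 104.3, so 105 per arm.

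This agrees with the stated 104 to within one patient; power at 104 is 79.9%. The figure uses 12-week rates only, so the 1-year rule does not touch it.

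**2. The two rules side by side.**

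| 12 weeks | 1 year | Any of four | With the 1-year rule |
|---|---|---|---|
| Cholesterol at target only | Cholesterol off target, stopped smoking | Success | Failure |
| No target met | Cholesterol off target, stopped smoking | Success | Success (no condition stated) |
| Three targets met | Two of the three kept | Success | Unclear |

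**3. Who faces the hurdle.** 54.8% of intervention and 35.6% of control patients, a ratio of 54.8 / 35.6 = 1.54.

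**4. Simple accounting.** Let p be the 12-week response rate, L the share of responders who lose the qualifying target, s the share of those who meet another at 1 year, and g the share of 12-week non-responders who meet any target at 1 year. Take L, s and g as equal in both arms.

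- Any of four: p(1 − L + Ls) + (1 − p)g
- With the rule: p(1 − L) + (1 − p)g

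The rule moves p × L × s of each arm from success to failure, so the difference shrinks by 0.192 × L × s. With L = 0.2, s = 0.5, g = 0.1:

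- Any of four: 53.8% vs 38.5%, difference 15.4 points, power at 104 per arm 60.5%.
- With the rule: 48.4% vs 34.9%, difference 13.4 points, power 50.2%.

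Over L from 0.1 to 0.4 and s from 0.1 to 0.75, the shrinkage runs from 0.192 × 0.01 = 0.2 points to 0.192 × 0.30 = 5.8 points.

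**5. A model that separates the readings.** Assume four independent, equally common factors, each with a latent normal correlation of 0.6 to 0.8 between visits. The chance q that a factor is at target at 12 weeks is 1 − (1 − 0.548)^(1/4) = 0.180 in the intervention arm and 1 − (1 − 0.356)^(1/4) = 0.104 in control. For one factor, let a be the chance of being at target at both visits, b at 12 weeks only, and d at neither.

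- One met target must hold: [1 − (1 − a)⁴] + [(1 − q)⁴ − d⁴]
- All met targets must hold: (1 − b)⁴ − d⁴
- 12-week non-responders cannot succeed: 1 − (1 − a)⁴

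Example: correlation 0.6, effect kept, all must hold. Intervention: b = 0.0940, d = 0.7259, giving 0.6738 − 0.2777 = 39.6%. Control: b = 0.0630, d = 0.8329, giving 0.7709 − 0.4811 = 29.0%.

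Differences in points, intervention minus control, from unrounded values:

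| Scoring at 1 year | Effect kept, 0.6 | Effect kept, 0.8 | Effect gone, 0.6 | Effect gone, 0.8 |
|---|---|---|---|---|
| Any of four | 19.2 | 19.2 | 0 | 0 |
| One must hold | 15.9 | 17.6 | −1.2 | −0.3 |
| All must hold | 10.6 | 13.0 | −5.4 | −5.4 |
| Non-responders cannot succeed | 14.7 | 16.7 | +5.8 | +6.3 |

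With the effect kept, power at 104 per arm is 79.9% for any of four, 65% to 73% if one must hold, and 36% to 49% if all must hold.

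**The case against.** The strongest defence is that this is a deliberate and disclosed durability rule: a general definition, then a specific provision for 1 year, which is reasonable after a 12-week programme. It stands in part, since wanting the gain to last is legitimate. But the text does not make a 12-week response a condition of 1-year success, so what is written is not sustained response.

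A second defence is that the criteria in the rule are simply the general definition. The wording points instead to the criteria by which that patient qualified at 12 weeks. If the general definition was meant, the sentence adds nothing and can go at no cost.

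A reader might infer that the rule biases the trial against the programme and can show harm where none exists. The documents do not support that as a general claim. The −5.4 points arise only if every met target must hold; even then a significant result at 104 per arm has a chance of about 14%. If one must hold, the figure is about −1 to 0. If 12-week non-responders cannot succeed, the sign reverses to about +6.

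Nor can a loss of planned power be claimed. The sample size rests on 12-week rates, no 1-year power is stated, and the model's prevalences and correlations are assumptions.

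**Conclusion.** The inconsistency is real and lies in the stated rule, not in something left to another document: two patients with identical 1-year status can receive opposite primary results because of their 12-week status.

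On the literal text, with similar loss and switching in both arms, the rule shrinks the 1-year difference. Its size cannot be found from the documents: 0.2 to 5.8 points in the simple accounting; in the four-factor model with the effect kept, from 19.2 to about 16–18 points (one must hold) or 11–13 (all must hold). With no remaining effect, the possible readings span about −5.4 to +6 points, so the direction depends on how the sentence is read. That alone shows that the 1-year endpoint is not fixed. The finding is confined to the 1-year comparison; the 12-week endpoint and the sample size stand.

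**What to change.** Before unblinding, score the 1-year primary endpoint for every patient from 1-year data, with the same any-of-four definition as at 12 weeks, and remove the added condition from the primary endpoint.

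Keep the durability question as a separate secondary endpoint, sustained response, in all randomised patients: at least one same factor at target at both 12 weeks and 1 year, with 12-week non-responders counted as not sustained. This also settles how patients with several targets are scored.

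The cost is a change of wording in the protocol and in the analysis plan. No new data are needed, since the 12-week and 1-year assessments already repeat the baseline measurements. The downside is that durability is no longer part of the 1-year primary endpoint and is reported as secondary.
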